## Abstract

**Background:**

Upper limb motor dysfunction is common after stroke and substantially restricts independence. Robot-assisted training (RAT) and blood flow restriction training (BFRT) have individually demonstrated potential benefits, but evidence regarding their combined application for upper limb rehabilitation after stroke remains limited.

**Objective:**

This study aims to investigate the effectiveness of RAT combined with BFRT in improving upper limb motor function among stroke survivors.

**Methods and analysis:**

This assessor-blinded randomized controlled trial will enroll 100 participants. Participants will be randomly assigned to one of four groups: (A) upper limb RAT combined with BFRT (UL-RAT + BFRT), (B) UL-RAT combined with sham BFRT, (C) BFRT combined with conventional occupational therapy, or (D) conventional occupational therapy alone. All interventions will be delivered once daily, 5 days per week, for 4 weeks. The outcome measures will include upper limb motor function assessed by the Fugl–Meyer Assessment, Upper limb and muscle strength, surface electromyography, Motricity Index–Upper Limb, grip strength, Action Research Arm Test, and Modified Barthel Index. Outcomes will be assessed at baseline and immediately after the intervention. Data will be analyzed according to the intention-to-treat principle, with statistical significance set at 0.05 (two-sided).

**Conclusion:**

This trial will evaluate the feasibility and potential effectiveness of combining BFRT with RAT for post-stroke upper limb rehabilitation.

**Clinical trial registration:**

https://www.chictr.org.cn/, identifier ChiCTR2500096611.

## Introduction

Stroke is a devastating cerebrovascular event and a leading cause of long-term disability in adults worldwide (1). Upper limb motor impairment is highly prevalent and represents a major barrier to functional independence following stroke (2). Effective upper limb performance relies on coordinated shoulder stability, wrist control, and hand dexterity. However, persistent muscle weakness substantially limits motor recovery and reduces quality of life (2, 3). Indeed, upper limb strength has been identified as one of the key predictors of functional outcomes after stroke (4). High-load resistance training [approximately 70% of one—repetition maximum (1RM)] is considered essential to induce significant muscle hypertrophy and strength gains within a relatively short period (5, 6). Nevertheless, stroke survivors frequently present limited cardiopulmonary capacity, abnormal muscle tone, deconditioning, and multiple comorbidities, which hinder their tolerance to high-intensity protocols (7). Therefore, developing low-load yet effective strength training strategies tailored to stroke survivors is of great clinical importance.

Blood flow restriction training (BFRT) is an innovative exercise method that partially restricts arterial inflow and venous return during physical activity by applying pneumatic cuffs proximally on the limbs (8, 9). This technique allows low-load resistance exercises to produce muscle hypertrophy and strength gains comparable to traditional high-load training (10). Although the precise mechanisms remain unclear, metabolic stress caused by hypoxic conditions, accelerated muscular fatigue, and activation of anabolic signaling pathways have been proposed as potential contributing factors (11, 12). BFRT offers advantages such as low cost, short training durations, and high tolerability, making it particularly valuable for individuals with limited exercise capacity (13). Studies involving healthy adults, athletes, and individuals recovering from upper limb injuries have demonstrated improvements in muscle strength, endurance, and morphological adaptations (14, 15). This makes it a promising option for neurorehabilitation.

Despite these advantages, the use of BFRT in stroke rehabilitation remains limited. Current clinical evidence predominantly addresses improvements in lower limb muscle strength and motor function (16–18). For example, Ahmed et al. reported that low-intensity BFRT significantly enhanced lower extremity strength and mobility in ischemic stroke survivors (16). Similarly, Li et al. observed beneficial effects of BFRT on lower limb muscles and motor Function in stroke patients (17). Recent investigations have begun exploring BFRT application for the upper limb after stroke. One randomized controlled trial protocol combining BFRT with muscle energy techniques to manage post-stroke upper limb spasticity has been published, but outcomes are not yet reported (19). To date, studies targeting the upper limb remain limited, and the therapeutic potential of BFRT for upper limb motor recovery after stroke is not fully stablished. Therefore, there is a critical need to identify effective and feasible BFRT-based strategies for upper limb rehabilitation in stroke patients.

Emerging evidence suggests that BFRT may influence motor recovery not only through peripheral muscular adaptations but also via central neurophysiological mechanisms. In patients with stroke, a recent functional near-infrared spectroscopy study has demonstrated that low-load BFRT significantly increases cortical activation in motor-related regions, including the primary motor cortex (M1) and premotor–supplementary motor areas (PMC–SMA) (20). Notably, these neural changes were positively correlated with improvements in motor performance, including Fugl–Meyer scores (20), suggesting a functional link between BFRT-induced cortical activation and motor recovery. Consistent findings from studies further indicate that BFRT can enhance cortical oxygenation, functional connectivity, and afferent feedback in a pressure-dependent manner (21, 22). In addition, BFRT may promote neuroplasticity through metabolic stress-induced upregulation of neurotrophic factors such as brain-derived neurotrophic factor (BDNF) (23). Collectively, these findings support a peripheral-to-central pathway, whereby BFRT may facilitate motor relearning by modulating corticospinal excitability and cortical network activity.

Upper limb motor dysfunction after stroke involves not only muscle weakness but also impaired motor control and coordination deficits. Interventions that can simultaneously enhance neural activation and support task-specific motor relearning may be particularly advantageous. Repetitive, task-specific training is critical for promoting motor learning and facilitating neuroplasticity (24, 25). However, most existing BFRT protocols emphasize lower limb activities such as squatting, resistance exercises, walking, or cycling, which lack sufficient relevance and engagement for patients with upper limb impairments. Robot-assisted training (RAT) provides intensity, repetitive, and task-oriented exercises within enriched, game-based environments, thereby enhancing patient motivation and adherence (26, 27). Additionally, its three-dimensional movement patterns, functional activities of daily living, improving joint coordination and neuromuscular control, and ultimately facilitating upper limb recovery (28, 29). Recent umbrella meta-analysis evidence supports RAT’s effectiveness in enhancing motor function and muscle strength in stroke patients motor function and muscle strength in stroke patients, although these improvements often fall short of clinically meaningful thresholds (30). Whether integrating BFRT with RAT could yield clinically significant enhancements remains unknown.

When integrated with RAT, which provides high-intensity, repetitive, and task-specific motor practice, BFRT-induced neural and neuromuscular adaptations may enhance motor learning processes. Specifically, BFRT may increase the responsiveness of the central nervous system to training stimuli, while RAT delivers structured, goal-directed practice necessary for skill acquisition and functional recovery. Therefore, the combination of BFRT and RAT may produce synergistic effects through the interaction of metabolic stress, neural activation, and task-specific motor learning. To our knowledge, no studies have yet evaluated their combined application for upper limb recovery after stroke. This protocol describes a randomized controlled trial designed to examine the feasibility, safety, and preliminary efficacy of this integrated intervention. We hypothesize that combined intervention will results in greater improvements in upper limb motor performance, muscle strength, and activities of daily living compared with RAT alone.

## Methods

### Study design

This single-center, four-arm, parallel-group randomized controlled trial will be conducted according to SPIRIT (Standard Protocol Items: Recommendations for Interventional Trials) guidelines and reported following the CONSORT (Consolidated Standards of Reporting Trials) statement. Outcome assessments will occur at: baseline (pre-intervention), immediately after intervention completion, and at a 4-week follow-up (Figure 1). The trial protocol received ethical approval from the Institutional Review Board of Wuxi Mental Health Center/Wuxi Central Rehabilitation Hospital (Approval No.: WXMHCIRB2024LLky017) and was prospectively registered with the Chinese Clinical Trial Registry (Registration No.: ChiCTR2500096611).

**Figure 1 fig1:**
[figure not shown]
CONSORT diagram. UL-RAT, upper limb—robot assisted therapy; BFR, blood flow restriction.

### Participants

Inclusion criteria: (1) diagnosis of stroke confirmed according to the Diagnostic Essentials of Various Cerebrovascular Diseases in China (2019 edition); (2) aged 40–80 years; (3) stroke onset within ≤6 months; (4) first-ever stroke resulting in unilateral hemiplegia; (5) Brunnstrom stage for upper limb >III; (6) Modified Ashworth Scale for upper limb <Grade II; (7) capable of following simple verbal instructions; (8) sitting balance level ≥2; and (9) signed informed consent form. Exclusion criteria: (1) upper limb venous thrombosis detected via ultrasound; (2) severe spasticity or significantly limited range of motion in the affected limb; (3) severe insufficiency of vital organs such as the heart, lungs, liver, or kidneys; (4) severe cognitive or communication impairments; (5) thrombocytopenia or coagulation disorders; (6) absence of skull integrity (e.g., following craniectomy); (7) large-area cerebral infarction or hemorrhage; and (8) current participation in other clinical trials.

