### Sample size estimate

Sample size was determined based on the primary comparison between the UL-RAT + BFRT group and the UL-RAT group. A minimal clinically important difference of 9 points on the Fugl-Meyer Assessment of the Upper Limb (FMA-UL) was adopted, which has been estimated for subacute stroke patients using anchor-based methods with the modified Rankin Scale (31). A standard deviation of 10 points was assumed, consistent with previous studies reporting FMA-UE scores in stroke populations (32). Using a two-sample t-test with a two-sided *α* of 0.05 and 80% power, the required sample size was calculated as 20 participants per group (G*Power 3.1.9.7). Although four parallel groups (UL-RAT + BFRT, UL-RAT, BFRT, and control) are included, additional groups primarily serve exploratory purposes. Assuming a 20% dropout rate, the total sample size was increased to 100 participants, resulting in 25 participants in each group.

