### Randomization and blinding

An independent researcher not involved in recruitment, intervention delivery, or outcome assessment generated a simple random allocation sequence via computer-based randomization at a 1:1:1:1 ratio. Group assignments were sealed in opaque, sequentially numbered envelopes prepared prior to the study and securely stored by the same researcher. After participants completed baseline assessments and eligibility was confirmed, a research assistant uninvolved in intervention or assessments opened the next sequential envelope privately and disclosed the assigned group on a sealed note to the therapist before the initial intervention session. Outcome assessors and data analysts will remain blinded to group allocation throughout data collection and analysis. Due to the nature of robot-assisted upper limb interventions, blinding of treating therapists is not possible.

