### Statistical analysis

Statistical analyses will be performed using SPSS version 22.0 (IBM Corp., Armonk, NY, United States). All analyses will follow the intention-to-treat principle. Baseline characteristics will be summarized using means ± standard deviations or median (interquartile ranges) for continuous variables, and frequencies (percentages) for categorical variables. Baseline group differences will be assessed using one-way analysis of variance, Kruskal–Wallis tests, or chi-square tests, as appropriate. A two-factor repeated-measures analysis of variance (group × time) will examine changes over time and group differences, provided assumptions are met. If normality or sphericity assumptions are violated, linear mixed-effects models will be applied. The primary analysis will focus on the between-group difference in change from baseline between the UL-RAT + BFR group and the UL-RAT group. Comparisons involving BFR and control groups will be exploratory. *Post hoc* pairwise comparisons with appropriate adjustments will be conducted when significant interactions or main effects are identified. A two-sided *p*-value < 0.05 will indicate statistical significance.

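### Time since stroke, open from onset to 6 months, is not in the stated primary model; prespecifying it as a covariate is a nearly free gain in precision, not the repair of a bias

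*Protocol article*

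**What the plan says.** All statements are in the Methods of the protocol article.

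- **Participants.** The only restriction on timing is "stroke onset within ≤6 months". No minimum interval is given.
- **Randomization and blinding.** An independent researcher "generated a simple random allocation sequence via computer-based randomization at a 1:1:1:1 ratio". No strata or blocks are mentioned. The list is described as already made and the envelopes as already prepared.
- **Statistical analysis, model.** "A two-factor repeated-measures analysis of variance (group × time) will examine changes over time and group differences, provided assumptions are met". The fallback is: "If normality or sphericity assumptions are violated, linear mixed-effects models will be applied". No covariate is named for either model.
- **Statistical analysis, primary contrast.** "The primary analysis will focus on the between-group difference in change from baseline between the UL-RAT + BFR group and the UL-RAT group".
- **Statistical analysis, baseline.** "Baseline group differences will be assessed using one-way analysis of variance, Kruskal–Wallis tests, or chi-square tests, as appropriate". What follows from those tests is not stated.
- **Sample size estimate.** "A minimal clinically important difference of 9 points on the Fugl-Meyer Assessment of the Upper Limb (FMA-UL) was adopted". The SD is 10, the test is an unadjusted two-sample t-test, 20 evaluable patients per group are required, and 25 per group are randomised.

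**The concern.** Patients may enter at any point in a six-month span, and the primary outcome is change over a four-week treatment period. If expected change over those four weeks differs between early and late entrants, time since stroke is prognostic for the primary outcome. Subtracting the baseline score removes a difference in starting level but not a difference in expected rate of recovery.

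Three features then combine. Simple allocation does nothing to balance this variable. The stated model has no term to absorb it. The arms being compared are small. A chance difference in mean time since stroke between A and B would therefore stay in the estimated effect, and the variation it explains would stay in the error term. The trial must establish time since onset to confirm eligibility, so it would be setting aside information that it already holds.

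**Working it through.** **1. The plan's own figure.** Inputs from Sample size estimate: difference 9, SD 10, two-sided alpha 0.05, power 80%.

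- n per group = 2 × (1.96 + 0.84)² × 10² / 9² = 19.4, so 20. This matches the article.
- The noncentral t distribution gives 79.2% power at 20 per group and 81.2% at 21, so the stated 20 is within one patient of the exact answer.
- Dropout: 20 / (1 − 0.20) = 25 per group, × 4 = 100. This also matches.

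**2. Assumptions the article does not supply.**

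- r, the correlation between time since stroke and 4-week FMA-UL change: range 0.1 to 0.5.
- The SD of 10 is taken as the SD of change.
- The relation is linear on the chosen scale.

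**3. Shift from chance imbalance, 20 per arm.** The standardised difference in mean time since stroke has SE = sqrt(2/20) = 0.316. The shift in A−B is r × 10 × imbalance. The adjusted residual SD is 10 × sqrt(1 − r²). Power is from the noncentral t with 37 degrees of freedom.

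| r | 1-SE shift (points) | 2-SE shift (points) | residual SD | power, adjusted |
|---|---|---|---|---|
| 0 | 0 | 0 | 10.00 | 79.1% |
| 0.1 | 0.3 | 0.6 | 9.95 | 79.6% |
| 0.3 | 0.9 | 1.9 | 9.54 | 82.8% |
| 0.5 | 1.6 | 3.2 | 8.66 | 89.3% |

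The unadjusted comparison has 79.2% power (38 degrees of freedom).

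**4. Simulation.** There were 10,000 trials per setting, with 20 per arm, time since stroke uniform on 0 to 6 months (an assumption), and R² = r².

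- Without adjustment the mean estimate under no effect is about 0, and type I error is 4.8% to 5.2% for R² from 0.10 to 0.40.
- Adjusted power is 82% at R² = 0.10 and 86% at R² = 0.20. The formula gives 83% and 87%, so it is optimistic by about one percentage point. At r = 0.1, adjustment is therefore roughly break-even.
- The difference in mean time since stroke has an SD of (6/sqrt(12)) × sqrt(2/20) = 0.55 months. About 7% of trials have arms that differ by a month or more. Within those trials the unadjusted type I error is about 9% at R² = 0.10 and 15% at R² = 0.20.

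**5. Sensitivity to the SD.** The article ties the 10 to FMA scores. If it is the SD of a score at each visit, the SD of change is 10 × sqrt(2(1 − ρ)), where ρ is the correlation between baseline and follow-up and is not given.

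- ρ = 0.5: the SD of change is 10, as in the table.
- ρ = 0.8: the SD of change is 6.3. The 1-SE shift for r = 0.3 to 0.5 is then 0.6 to 1.0 points. Unadjusted power for 9 points is already about 99%, so there is almost no power left to gain.

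**The case against.** The strongest reply is that nothing here is wrong. Under simple randomisation the unadjusted comparison is unbiased and keeps its level, as step 4 confirms, and its standard error already allows for chance imbalance in every prognostic variable. This stands. A reader might infer from the wide window and unstratified allocation that the A−B estimate is biased or the test invalid. The article does not support that reading.

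Second, covariates are often left to a statistical analysis plan, and the article nowhere forbids them. This stands in part. A reader should not take silence as a prohibition, and the mixed-model fallback could carry further terms. But the article does state the model, its factors, the fallback and the primary contrast, and it describes the main analysis as two-factor. That stated choice can fairly be improved.

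Third, the article never says that recovery depends on time since stroke. The other entry criteria (Brunnstrom stage, spasticity, sitting balance, exclusion of large lesions) might weaken any such link. This stands: r is assumed, and low values must be part of the range.

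Fourth, the size is easily overstated. A shift of 1.9 to 3.2 points, or 21% to 35% of the target, needs a 2-SE imbalance, which arises in roughly 5% of trials. The SD of 10 may not be the SD of change. The power gain was computed for time since stroke alone, not as an addition to baseline FMA-UL, where it may be smaller. All of this stands. So does the remark that a straight line in days would fit a fast-then-flat recovery only roughly.

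**Conclusion.** The point holds as an efficiency recommendation. The stated model omits a baseline variable that the trial already collects, that its entry window allows to vary widely, and that its allocation does nothing to balance. If this variable predicts 4-week change, the unadjusted analysis loses precision and is exposed to conditional error after an unlucky allocation. The typical shift is 0.3 to 1.6 points, and power is about 80% to 89% with adjustment against 79% without. These figures assume r of 0.1 to 0.5, an SD of change of 10, 20 per arm and linearity. They shrink if change varies less than that or if baseline FMA-UL already explains part of the variation, and at the low end of r the gain is negligible.

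The stated sample size is not undermined, and no systematic bias is shown. The case for acting rests on the low cost and on the need to decide beforehand: a covariate added after the planned baseline tests have been seen would be a data-driven choice.

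**What to change.** In Statistical analysis, prespecify the primary A versus B analysis as an ANCOVA or linear mixed model for FMA-UL, with baseline FMA-UL and time from stroke onset to randomisation as fixed covariates. Fix the functional form of the time term in advance, for example log days. State that both covariates stay in the model whatever the baseline significance tests show.

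The cost is a sentence or two of analysis text and one degree of freedom for the time term. If r is 0, that degree of freedom takes power from 79.2% to 79.1%; the simulation suggests an average loss nearer one point once chance imbalance is counted. No new assessment is needed, because eligibility already requires the timing of onset, and mixed models are already planned in the named software. The sample size, the allocation list and the treatments are untouched. Stratifying by time since stroke would be an alternative only if the list, described as already generated, could still be replaced.

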### Sample size estimate

Sample size was determined based on the primary comparison between the UL-RAT + BFRT group and the UL-RAT group. A minimal clinically important difference of 9 points on the Fugl-Meyer Assessment of the Upper Limb (FMA-UL) was adopted, which has been estimated for subacute stroke patients using anchor-based methods with the modified Rankin Scale (31). A standard deviation of 10 points was assumed, consistent with previous studies reporting FMA-UE scores in stroke populations (32). Using a two-sample t-test with a two-sided *α* of 0.05 and 80% power, the required sample size was calculated as 20 participants per group (G*Power 3.1.9.7). Although four parallel groups (UL-RAT + BFRT, UL-RAT, BFRT, and control) are included, additional groups primarily serve exploratory purposes. Assuming a 20% dropout rate, the total sample size was increased to 100 participants, resulting in 25 participants in each group.

### Randomization and blinding

An independent researcher not involved in recruitment, intervention delivery, or outcome assessment generated a simple random allocation sequence via computer-based randomization at a 1:1:1:1 ratio. Group assignments were sealed in opaque, sequentially numbered envelopes prepared prior to the study and securely stored by the same researcher. After participants completed baseline assessments and eligibility was confirmed, a research assistant uninvolved in intervention or assessments opened the next sequential envelope privately and disclosed the assigned group on a sealed note to the therapist before the initial intervention session. Outcome assessors and data analysts will remain blinded to group allocation throughout data collection and analysis. Due to the nature of robot-assisted upper limb interventions, blinding of treating therapists is not possible.

